### Loading doses

The loading dose is based on half-life. Clonidine follows first order kinetics for elimination, and thus the mean steady state is proportional to the daily dose. Doubling the total daily dose should double the mean plasma concentration level. A study showed that a single oral dose of 75ug clonidine gave Cmax 0.29 ng/ml, 150ug gave Cmax 0.61 ng/ml and 250ug gave 1.2 ng/ml [45]. We will administer up to 300 μg the first day, but as 75 ug every three hours. Thus, the theoretical Cmax at day one would be significantly lower than 1.2 ng/ml, due to elimination of the drug. How much lower is difficult to estimate, given the large variability in half-life (5 to 25 hours).

The expected maximum hypotensive effect correlates well with the Cmax time-point occurring after 2 hours. There is an interindividual difference in the pharmacodynamic response to clonidine. Our loading dose is dependent on and monitored by the individual patients' haemodynamic response (blood pressure and heart rate).

### Safety review

A safety review will be done after we have recruited 20 patients (10 placebo and 10 clonidine). Recruitment of the additional 80 patients will be halted until we have made an assessment of the serum concentration levels, pharmacokinetics and -dynamics (the haemodynamic response) in these initial 20 patients. These data will then guide further dosage for the subsequent 80 patients. We are aiming for serum concentration levels between 0.3 and 0.7 ng/ml, but may accept a small number of single measures above this range. Blood samples for serum concentration measurement will be taken 3 hours after the patient has taken the study drug (each time) on day 1 and just before administration of study drug between 0800 and 0900 on day 2. The serum concentration levels and pharmacodynamic responses will be assessed by an independent Data Monitoring Committee. The determination of the further dosage plan will thus be based on both pharmacokinetics/serum concentration levels and the individual patients´ haemodynamic responses. The further dosage plan will be approved by The Norwegian Medicines Agency.

## Study objectives

### Primary endpoint

The endpoints and measurements for efficacy assessment are listed in Table 2. Our primary objective is to explore the potential superiority of clonidine vs placebo in decreasing delirium duration and severity, measured by Memorial Delirium Assessment Scale (MDAS) [58] in patients diagnosed with delirium or subsyndromal delirium (according to Diagnostic and Statistical Manual of Mental Disorders, DSM-5 [59]). The primary endpoint, the trajectory of delirium, is the severity of delirium (measured by MDAS) over time.

**Table 2 Tab2:** **List of endpoints and measurements for efficacy assessment**

Endpoint	Measurements for efficacy assessment
**Primary**	
Delirium trajectory	MDAS
**Secondary** (also with subanalyses for subsyndromal delirium and hypoactive/hyperactive/mixed delirium)	
Time-to-first delirium resolution	DSM-5
Incidence of “full-scale” delirium	DSM-5
Severity of delirium	MDAS, OSLA
Delirium subtype	MDAS, OSLA, DelApp
Use of “rescue medication”/additional drugs (as other sedatives, analgetics and antipsychotics)	Registration of use of all medication
Length of hospital stay	Registrations
Patient distress	Checklist of Nonverbal Pain Indicators
Cognitive function in follow-up after 4 months	MMSE-NR, Clock drawing test, Ten-words memory test, Trial making test A and B, IQCODE, CDR
Independence in follow-up after 4 months	Barthel ADL, NEADL
Pharmacokinetic response to clonidine	Serum drug concentrations
Pharmacodynamic response to clonidine	BP, HR, ECG, RASS, OSLA, symptoms of bradycardia, orthostatic hypotension or other side-effects
Biomarkers	Blood samples
Institutionalisation	Registrations
Survival	Registrations
**Safety**	
Side effects of clonidine/in-hospital complications	BP, HR, ECG, sedation (RASS, OSLA), and any symptoms of bradycardia, orthostatic hypotension or other side-effects

### Secondary endpoints

We will compare the actively treated group with the placebo group with respect to secondary endpoints shown in Table 2. The main secondary endpoint is the duration of delirium monitored daily by the DSM-5 diagnostic criteria. We will also study the feasibility of oral clonidine in a geriatric ward and effects of clonidine upon a variety of outcomes as a means to design a potentially more definite study later. We will do per protocol analyses and exposure-response analyses based on plasma-concentration.

## Methods and design

### Study design

The Oslo Study of Clonidine in Elderly Patients with Delirium (LUCID) is a randomised, placebo-controlled, double-blinded, parallel group study with 4 month prospective follow-up (Figure 1). We aim to include 100 inpatients with delirium (or subsyndromal delirium) in an acute geriatric ward. Patients will be randomised to orally administrated clonidine or placebo until delirium free (by DSM-5 criteria) or no subsyndromal delirium for 2 days, or after a maximum of 7 days treatment. If the treating physician plan to discharge the patient (still having delirium/subsyndromal delirium), before 7 days, we will end the treatment 24 hours before discharge. Assessment of haemodynamics (blood pressure, heart rate and ECG) and of delirium will be performed daily until discharge, or a maximum of 7 days after end of treatment.

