### Monitoring and safety

BP and HR will be monitored 3 hours after each loading dose (day 1) and then just before every dose. If there are signs of significant hypotension (systolic BP <100 mmHg) or bradycardia (heart rate <50 beats/min), further monitoring or treatment will be considered individually. During the whole treatment period blood pressure and heart rate will be assessed twice per day. ECG, serum creatinine, blood glucose and a clinical assessment by a physician (hydration, side-effects, RASS [61] and OSLA [62]) will be performed daily. Orthostatic BPtests will be performed during the hospital stay at day 5, 6 or 7 at 1100 (approximately 3 hours after administration of study drug).

For all patients, drug concentration (mean concentration just before intake and Cmax 3 hours after intake) will be measured at day 5, 6 or 7. The pharmacokinetics of clonidine varies inter-individually, possibly influencing individual treatment responses. But due to the short treatment period, measurement of drug concentration for individual drug modification is not feasible.

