### Laboratory tests and blood sample procedures

Data from routine blood samples taken at admission will be recorded (including Erythrocyte Sedimentation Rate, Haemoglobin, Leukocytes, Creatinine, Electrolytes, C-reactive protein, Albumin, Thyroid stimulating hormone and free Thyroxine levels).

All patients will have blood drawn for drug concentration levels at day 5, 6 or 7 (just before and 3 hours after intake of study medication), to be able to compare possible effects and side-effects to the actual plasma-concentration at the end of the trial.

Our study population is expected to have significant acute and chronic comorbidity. In this aspect, looking for new biomarkers is challenging, as we do not have a delirium-free control group. We will however take blood samples (serum and plasma) for biomarkers at inclusion, at mid-stay (day 3–5) and at discharge, to explore markers already known to be associated with delirium. Interesting biomarker candidates include S100B [80,81], neopterin [82], IGF-1 [83], MMP-9, protein C, sTNFR1 [84]. The serum and plasma will be stored in a biobank freezer at Oslo University Hospital together with blood stored in EDTA tubes for possible DNA-analyses.

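### Drug levels and the orthostatic blood pressure test are fixed on day 5 to 7 on drug, but treatment can end on day 3 or 4, so early stoppers miss both

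*Protocol article*

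**What the plan says.** All references are to the protocol article.

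- **Stop rule.** Under Study design, treatment continues "until delirium free (by DSM-5 criteria) or no subsyndromal delirium for 2 days, or after a maximum of 7 days treatment". The same paragraph ends treatment 24 hours before discharge when a patient who still has delirium or subsyndromal delirium is to leave before 7 days. The abstract gives the rule for DSM-5 delirium only.
- **Drug levels.** Monitoring and safety: "For all patients, drug concentration (mean concentration just before intake and Cmax 3 hours after intake) will be measured at day 5"; the two following days are allowed as alternatives. Laboratory tests and blood sample procedures repeats this: "All patients will have blood drawn for drug concentration levels at day 5, 6 or 7 (just before and 3 hours after intake".
- **Orthostatic test.** Monitoring and safety: these tests "will be performed during the hospital stay at day 5, 6 or 7 at 1100 (approximately 3 hours after administration of study drug".
- **Earlier levels.** Safety review takes samples "3 hours after the patient has taken the study drug (each time) on day 1 and just before administration of study drug" on the morning of day 2. This is for the first 20 patients, 10 of them on clonidine.
- **Use of the levels.** Secondary endpoints: "We will do per protocol analyses and exposure-response analyses based on plasma-concentration".

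**The concern.** The level pair and the orthostatic test both need a patient who takes a dose on day 5 or later. The stop rule removes some patients from drug before that, and the article describes no earlier sample or test for them. These are stated rules that cannot all be followed, not a detail left out.

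Whether a level exists then depends partly on how fast the patient improved, and improvement is the response side of the exposure-response analysis. Losing the fastest improvers narrows the response range and can weaken or distort any relation with concentration. The orthostatic test is left on a subset chosen partly by response. If clonidine shortens delirium, that subset differs between the arms.

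**Working it through.** **1. Last treatment day.** Delirium is assessed daily. Let d be the first clear day, with day 1 the loading day. If 2 days means two consecutive clear daily assessments, the last treatment day is d + 1. If it means 48 hours from the first clear assessment, it is d + 2.

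| First clear day | Two assessments | 48 hours | Intake on day 5 to 7? |
|---|---|---|---|
| 2 | day 3 | day 4 | no under either count |
| 3 | day 4 | day 5 | no; under 48 hours it depends on the hour |
| 4 | day 5 | day 6 | yes |

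This holds whether clear means free of DSM-5 delirium or free of subsyndromal delirium as well. Discharge on day 5 minus 24 hours puts the last dose on day 4, so any discharge on or before day 5 has the same effect.

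**2. Who has no level at all.** Assuming 1:1 allocation, 50 of the 100 patients receive clonidine. Ten of them are in the first 20 and have day 1 and 2 levels. The other 50 − 10 = 40 have only the day 5 to 7 pair. Each 10% of these who stop before day 5 is 0.10 × 40 = 4 patients with no level.

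**3. Possible share lost (illustration).** The article gives no figure for this. Its only recovery figures are 40% versus 65% in the sample size section. With 50 per arm, two-sided 5% and pooled variance, they give (0.25 − 1.96 × 0.0999) / 0.0967 = 0.56, which is 71.3% power against the stated 71%. No time point is attached to these rates. Assume they are reached by day 7 at a constant daily rate h over six daily steps (days 2 to 7): h = 1 − (1 − p)^(1/6) = 0.082 (placebo) and 0.161 (clonidine).

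- First clear by day 2 (lost under the 48-hour count): 8% and 16%.
- First clear by day 3 (lost under two assessments), 1 − (1 − h)²: 16% and 30%.

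If the rates are reached only by day 14 (13 steps), the figures are 4% and 8%, and 8% and 15%. For 50 clonidine patients this spans about 4 to 15, before early discharges.

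**4. Effect on a level-response correlation (illustration).** Assume a bivariate normal relation with true correlation 0.30, and remove the fastest share p. With c = z(1 − p) and L = φ(c)/(1 − p), the remaining response variance is u² = 1 − cL − L², and r′ = 0.30u / √(0.91 + 0.09u²).

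| p | u² | r′ |
|---|---|---|
| 5% | 0.810 | 0.27 |
| 10% | 0.712 | 0.26 |
| 20% | 0.583 | 0.23 |
| 30% | 0.493 | 0.22 |

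**5. How comparable an early level is.** The model has one compartment, first-order elimination and immediate absorption. Doses follow Table 1: 75 μg at 14, 17, 20 and 23 h on day 1, then at 08:30 and 20:30. Half-life runs over the article's range of 5 to 25.5 h. Pre-dose level relative to day 6:

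| | Day 3 | Day 4 |
|---|---|---|
| Four loading doses | 1.03–1.20 | 1.00–1.06 |
| One loading dose | 0.64–0.98 | 0.84–1.00 |

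**The case against.** - **Late sampling has a purpose.** The laboratory section wants concentrations from the end of treatment, and day 5 is closer to steady state. In the model above, the day 5 pre-dose level is about 0.95 to 1.01 times the day 6 level with one or four loading doses, against 0.64 to 1.20 on day 3. This stands as a reason to keep day 5 to 7 as the default. It does not justify having no level for early stoppers.
- **Early sampling keeps a link to response.** Sampling day would then depend on speed of improvement. This also stands, and is why sampling day and loading doses must be recorded and a day 5 to 7 sensitivity analysis kept. A level with its day recorded is still better than none.
- **The effect is small and the analysis exploratory.** The illustrated fall of 0.03 to 0.08 is below the standard error of a correlation of 0.30 in 50 patients, (1 − 0.09)/√49 = 0.13. The Discussion calls the secondary objectives exploratory. This limits the weight of the point but does not remove the conflict.
- **Safety is well covered otherwise.** A reader might infer that early stoppers drop out of the safety comparison. They do not. The safety row of Table 2 covers BP, HR, ECG, "sedation (RASS, OSLA), and any symptoms of bradycardia, orthostatic hypotension or other side-effects". Early stoppers keep BP and HR around the loading doses and before every dose, the daily ECG and clinical assessment while on drug, and the telephone call a week after treatment. What they lose is the one scheduled postural test.
- **The article is condensed.** A full protocol may handle early stoppers. But the article fixes the days and says all patients, in two sections, so the conflict is in what is stated.

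**Conclusion.** The point holds in a limited form. As written, patients who stop on day 3 or 4 miss the day 5 to 7 levels and the only scheduled orthostatic test, and the loss depends partly on response. Early discharge of patients who have not recovered contributes too. It can bias the exploratory exposure-response analysis and leaves the orthostatic test on a response-selected subset. An imbalance between arms in that test would arise from the stop rule only if clonidine does shorten delirium.

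The size is not known. The shares in step 3 and the correlation in step 4 are assumptions, and the ratios in step 5 assume Table 1 dosing, which the safety review may change for the last 80 patients.

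Three stronger readings are not supported:

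- That early improvers have no drug level at all. The first 20 patients have day 1 and 2 levels, although these come from the loading phase.
- That the primary comparison is biased. It does not use the levels or the orthostatic test.
- That a patient with subsyndromal delirium meets the stop rule on entry. The word 'or' under Study design allows this literally, and would put the gap at 3 versus 7 days of drug (300 + 2 × 150 = 600 μg versus 300 + 6 × 150 = 1,200 μg). But the Study population section, the inclusion criteria and the discharge sentence all treat subsyndromal delirium as a state to be treated, so the rule points to freedom from both. The wording is a minor clarification.

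This should be changed because it is cheap, but it does not threaten the main result.

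**What to change.** In Monitoring and safety and in Laboratory tests and blood sample procedures, for both the level pair and the orthostatic test, write: *on day 5, 6 or 7, or, if the first clear day falls before day 4 or discharge is planned on or before day 5, around the next morning dose while still on drug*. The first clear day is known the day before that dose. A patient sampled early who relapses and stays on drug has the day 5 to 7 pair as well.

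Record the sampling day and the number of loading doses taken, use both in the exposure-response analysis, and add a sensitivity analysis limited to day 5 to 7 levels.

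As a clarification, word the stop rule under Study design and in the abstract as: *until free of both DSM-5 delirium and subsyndromal delirium for 2 consecutive days, or a maximum of 7 days*.

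Cost: wording only, and no extra patients. The article already plans "blood samples (serum and plasma) for biomarkers at inclusion, at mid-stay (day 3–5) and at discharge", so the early pre-dose sample can join the mid-stay draw. The 3-hour sample is moved earlier rather than added for patients who do stop early. The downside is that day 3 and 4 levels are less comparable (pre-dose about 0.64 to 1.20 times the day 6 level under Table 1 dosing). A discharge decided too late for another morning dose will still lose the sample.

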**Figure 1 Fig1:**
[figure not shown]
**CONSORT Study flow diagram.**

This study will be conducted in compliance with the Declaration of Helsinki and with ICH/Good Clinical Practice. Registration of patient data will be carried out in accordance with national personal data laws. The study design, protocol and informed consent procedures are approved by the Regional Medical Ethics Committee and the Norwegian Medicines Agency (EUDRACT number 2013-000815-26). The study is also registered at www.clinicaltrials.gov (NCT01956604).

### Study population

We will recruit patients >65 years of age from the acute geriatric ward at Oslo University Hospital. These patients are usually acutely admitted, arriving directly from the emergency department, with considerable multimorbidity and polypharmacy, with a high prevalence of infections, dehydration, acute cardiac problems, general medical problems, functional decline and delirium. They might be included at admission (prevalent delirium), or during the stay (incident delirium). Patients with prevalent delirium/subsyndromal delirium must be included within approximately 48 hours after admission and patients with incident delirium/subsyndromal delirium must be included within approximately 48 hours of symptom onset. All patients must have current delirium/subsyndromal delirium at the time of inclusion.

### Screening

Patients admitted to the study ward will go through a simple screening process (see Table 3). This screening is a combination of the Single Question in Delirium (SQiD) (asking one question to the patient's friend or relative:” Do you think (name) has been more confused in the last two weeks?”) [60], combined with two simple attention tests (reciting the days of the week and months of the year backwards). If any of these tests are positive, if the patient is drowsy, or if the nurse and/or the treating physician for other reasons suspects delirium, ascertainment of delirium or subsyndromal delirium will be performed.

**Table 3 Tab3:** **Screening for delirium in patients at the acute geriatric ward**

		Yes	No
Screening	SQiD	□	□
	Drowsiness	□	□
	Cannot recite months backwards (unable to reach July)	□	□
	Cannot recite all the weekdays backwards	□	□
	Staff suspect delirium	□	□
Ascertainment of delirium or subsyndromal delirium	If Yes in any box, do diagnostic procedure (DSM-5), Table 4		
Inclusion	All DSM-5 criteria (delirium) or subsyndromal delirium → can be included		
	If the patient meets all the inclusion criteria, the patient will be included		

### Diagnosis of delirium and subsyndromal delirium

The diagnosis of delirium will be made by the study physicians according to DSM-5 criteria by using a standardised procedure (Table 4). Level of arousal will be assessed using the Richmond Agitation and Sedation Scale (RASS) [61] and the Observational Scale of Level of Arousal (OSLA) [62]. Attention will be evaluated using objective tests (Table 4) and observations by the examiner of the patient´s distractibility, comprehension and tendency to lose the thread of conversation. We will also use a smartphone (Android) software application, the “DelApp” [63], which incorporates an initial test of level of arousal followed by a test of attention. Acute change in the patient´s mental status, and fluctuation of any disturbance, will be ascertained through informant history from nursing staff and carers and also derived from clinical notes. Assessment of additional mental status disturbances will be performed by asking the patient a list of pre-defined questions (Table 4) in addition to information derived from nursing staff and clinical notes. All these assessments will be used in combination in relation to the DSM-5 criteria. The objective indicators (described above and in Table 4) will be supplemented by the assessor´s judgement regarding subjective features and a final diagnosis made.

**Table 4 Tab4:** **Diagnostic algorithm for DSM-5 delirium**

DSM-5 criteria	Tests to be performed or information needed			DSM-5 criteria fullfilled?	
				YES	NO
A. Disturbance in attention (i.e., reduced ability to direct, focus, sustain, and shift attention) and awareness (reduced orientation to the environment).	**Evaluation**	**TEST**	**Cut off (definition of inattention)**		
	**Daily**	Digit span forward	Less than 5 forward		
	**Daily**	Digit span backward	Less than 3 backwards		
	**Daily**	SAVEAHAART	2 or more errors		
	**Initial diagnosis only**	Days of the week in reverse order	Any error		
	**Initial diagnosis only**	Months of the year in reverse order	Unable to reach July		
	**Initial diagnosis only**	Count backwards from 20 to 1	Any error		
	Observation (by the examiner):				
	Distractibility. Comprehension. Tendency to lose the tread of conversation				
	The “DelApp” [level of arousal test followed by counting of serially-presented lights. Cut-off 7/8 out of 10]				
B. The disturbance develops over a short period of time (usually hours to a few days), represents a change from baseline attention and awareness, and tends to fluctuate in severity during the course of a day.	Informant history from patient´s carers and nursing staff				
	Questions to carer/ nursing staff or derived from clinical notes:				
	Has there been a sudden change in the patient´s mental state?				
	Does the patient seem to be better at any period in the day compared to other times?				
	Has the level of consciousness been altered (drowsy/not interacting or agitated)?				
	Sleep-wake cycle disturbances?				
C. An additional disturbance in cognition (e.g., memory deficit, disorientation, language, visuospatial ability, or perception).	Questions to the patient:				
	Orientation to time, place and person				
	Recall (3 words)				
	Why are you in hospital? Will a stone float in water? Are there fish in the sea? (any error = disorganised thinking)				
	Questions to carer/ nursing staff or derived from clinical notes:				
	Has there been any…:				
	Perceptual disturbances? Sleep-wake cycle disturbances? Memory disturbances? Psychotic symptoms?				
	Psychomotor abnormalities?				
D. The disturbances in criteria A and C are not explained by another preexisting, established, or evolving neurocognitive disorder and do not occur in the context of a severely reduced level of arousal, such as coma.	Information from history/chart/clinical assessment				
E. There is evidence from the history, physical examination, or laboratory findings that the disturbance is a direct physiologic consequence of another medical condition, substance intoxication or withdrawal (i.e., because of a drug of abuse or to a medication), or exposure to a toxin or is because of multiple etiologies.	Information from history/chart/clinical assessment				
Delirium based on the tests and information above?	All DSM-5 criteria fulfilled			Yes □	No □
Subsyndromal delirium based on the tests and information above?	Defined as evidence of change, in addition to any one of these: (a) altered arousal, (b) attentional deficits, (c) other cognitive change, (d) delusions or hallucinations.			Yes □	No □
	Criteria D and E must be met.				

Subsyndromal delirium will be defined as evidence of change, in addition to any one of these: (a) altered arousal, (b) attentional deficits, (c) other cognitive change, (d) delusions or hallucinations. DSM-5 criteria D and E must be met. The severity of delirium will be assessed for all included patients by MDAS [58], based on the tests and information described above. We will also register the Confusion Assessment Method (CAM) [64] daily.

